### Sample size calculations

The primary outcome will be differences between the groups in the number of participants who have received surgical treatment after 2 years. Calculation of sample size is based on the assumptions that at least 70% of those who are currently deemed eligible for surgery will undergo operations, and that the number of operations in the intervention group will be equal to or less than that of the control group (one-sided calculation). To be able to detect a difference of 20% in surgery rate between the groups, with a power of 80%, a significance level of 0.05 and a 20% dropout rate, a total of 180 participants (90 in each group) will be needed.

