### Statistical analyses

The main treatment analysis will be conducted blinded to treatment allocation and will be analysed on an intention-to-treat basis with all randomized participants retaining their original randomized group. In the analysis of the primary outcome, the number of participants in each group who have received surgical treatment after 2 years will be compared using binary mixed models logistic regression and presented as odds ratios with a 95% CI.

We will also use mixed Cox proportional hazard models to describe and compare time to operation in the two groups, including establishment of the vital assumption of proportionality of the hazard rates.

In terms of secondary and tertiary outcomes, differences in mean values with 95% CI at each follow up will be analysed using mixed models analysis of covariance, adjusting for baseline levels of the outcome measure, while generalized linear mixed models will be used to estimate the overall effect for the total 2-year trial period, adjusting for the effect of clustering and repeated measures over time.

The assessment of the psychometric properties of MAP-Hand (research question 4) will adhere to the methods recommended by the international COSMIN group, using Kappa and ICC for examining test-retest reliability, and an anchor-based approach (based on the five-point global rating scale) to determine the minimal important change [62]. The smallest detectable change will be assessed by examining limits of agreement of repeated measures, computed as ± 1.96 SD of the difference between baseline scores and retest scores. The results from participants who report change in disease activity between baseline and rescoring will be excluded from the analysis of test-retest reliability and the smallest detectable change.

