To assess the cost-effectiveness, we will need to estimate health outcomes and costs. The health outcomes will be measured using the EQ-5D and the costs will include the cost of the two interventions. This comprises the hours and frequency of occupational therapy, costs related to the provision of assistive devices, orthoses, and exercise material, and costs related to the surgical procedures, including post-operative treatment. Furthermore, costs related to medical or technical equipment purchased by participants and to the use of other health care services (home care services, rehabilitation, and institution) will be recorded for both the intervention and control group during the trial period.

Standard methods for economic evaluation will be applied and the cost-effectiveness will be calculated as the incremental cost-effectiveness ratio, which is defined by the cost per incremental QALY.

The level of significance will be set to 0.05 and we will use IBM SPSS Statistics 21 (IBM Corporation), R (R Core Team (2016). R: A language and environment for statistical computing. R Foundation for Statistical Computing, Vienna, Austria.) and Statistical Analysis System (SAS Institute Inc., Cary, NC, USA).

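### The 80% power claimed for 180 participants holds only for a one-sided 5% test; for the two-sided 95% CI that is planned, power is about 70%

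*Protocol article*

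**What the plan says.** Under Sample size calculations, the protocol article defines the endpoint as binary: "The primary outcome will be differences between the groups in the number of participants who have received surgical treatment after 2 years". Its planning inputs are:

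- a surgery rate in which "at least 70% of those who are currently deemed eligible for surgery will undergo operations";
- a target stated as "To be able to detect a difference of 20% in surgery rate between the groups";
- error rates and attrition given as "with a power of 80%, a significance level of 0.05 and a 20% dropout rate";
- a directional premise, "that the number of operations in the intervention group will be equal to or less than that of the control group (one-sided calculation").

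The result is that "a total of 180 participants (90 in each group) will be needed".

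Under Statistical analyses, the groups "will be compared using binary mixed models logistic regression and presented as odds ratios with a 95% CI". That section closes with one general rule: "The level of significance will be set to 0.05". It does not mention sidedness, and the article has no one-sided test, one-sided confidence bound or 90% interval.

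**The concern.** A 95% CI for the odds ratio excludes 1 when a two-sided 5% test rejects. A one-sided 5% test corresponds to the 90% CI. The trial is therefore sized on one criterion and reported on a stricter one, and the 80% power belongs only to the first.

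Two things are at stake. First, the stated power is too high for the analysis that readers will see. Second, some results would count as success on the sizing criterion and as failure on the reporting criterion. If the primary result fell there, the document would support either reading, and sidedness could end up being settled with the data in view. The Discussion says that a proven intervention should become mandatory before surgery is considered, so the rule for calling it effective needs to be unambiguous.

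**Working it through.** **Inputs** (all from Sample size calculations): control rate p1 = 0.70; intervention rate p2 = 0.50 (20 points lower); alpha = 0.05; power 0.80; dropout 0.20; 90 randomised per arm, so 90 × 0.8 = 72 evaluable per arm.

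The sum of variances is 0.70 × 0.30 + 0.50 × 0.50 = 0.21 + 0.25 = 0.46. The squared difference is 0.20² = 0.04.

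**Step 1. Reproduce the plan's figure, one-sided.**
n per arm = (z_alpha + z_power)² × 0.46 / 0.04.
- Unpooled: (1.645 + 0.842)² × 0.46 / 0.04 = 71.1, so 72 evaluable; 72/0.8 = 90 per arm, 180 in total. This is an exact match.
- Pooled variance under the null: 73.1 per arm; 73.1/0.8 = 91. This is close to 90.
- A relative 20% reduction (0.70 to 0.56) does not fit. One-sided and unpooled, it needs 144 evaluable per arm, and 144/0.8 = 180 per arm, or 360 in total.

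**Step 2. The same inputs, two-sided** (1.960 in place of 1.645).
- Unpooled: (1.960 + 0.842)² × 0.46 / 0.04 = 90.3, so 91 evaluable; 91/0.8 = 113.75, so 114 per arm, 228 in total.
- Pooled: 93.0, so 93 evaluable; 93/0.8 = 116.25, so 117 per arm, 234 in total.

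Neither is near 180, so 180 rests on the one-sided calculation.

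**Step 3. Power at 72 evaluable per arm.**
Unpooled: SE = √(0.46/72) = 0.0799 and 0.20/0.0799 = 2.502. One-sided power = Φ(2.502 − 1.645) = 0.804. Two-sided power = Φ(2.502 − 1.960) = 0.706.

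| Method | One-sided 5% | Two-sided 5% |
|---|---|---|
| Unpooled normal | 80.4% | 70.6% |
| Pooled normal | 79.4% | 69.1% |
| Exact enumeration, score test | 80.3% | 69.6% |
| Exact enumeration, Wald test of log odds ratio | 80.3% | 69.6% |

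**Step 4. Difference detectable with 80% two-sided power at 72 per arm, control rate 70%.** This is 22.4 points unpooled and 22.8 pooled. By exact enumeration of the score test, power is 77.6% at 22 points and 81.1% at 23 points.

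**Step 5. A result between the two criteria.** Suppose 50/72 controls and 40/72 intervention participants have surgery. The odds ratio is (40/32)/(50/22) = 0.55. The SE of its log is √(1/40 + 1/32 + 1/50 + 1/22) = 0.349. The 95% CI is 0.28 to 1.09, which includes 1. The one-sided p is 0.043 and the 90% CI is 0.31 to 0.98, which excludes 1.

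**Step 6. Sensitivity of two-sided power.**
- No loss, 90 analysed per arm: 78.7% pooled, 79.9% unpooled.
- 72 per arm, same 20-point difference, pooled: 71.5% at a control rate of 75%, 75.0% at 80%, 79.8% at 85%.

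These figures ignore clustering by centre in the mixed model.

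**The case against.** The strongest reply is that nothing is miscalculated. The one-sided basis is disclosed, 180 follows from it, and 80% power is correct for that calculation. The analysis section never says two-sided, a 95% CI may be only a reporting format beside a one-sided test, and the full protocol or SAP may state the decision rule. Power would also be better if surgery status were obtained for everyone randomised, as the intention-to-treat plan implies, or if the control rate exceeded 70%.

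Part of this stands. The sizing arithmetic is right taken alone; the fault lies between the two sections. The two-sided reading is inferred, though it is the conventional one. With complete ascertainment the shortfall nearly disappears.

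The rest does not remove the problem. If a one-sided 5% test is intended, the unqualified 95% CI is the wrong interval for it, so a correction is needed on either reading. The article itself plans for 20% dropout and sizes at 70%, so its power claim must be judged at 72 per arm. A control rate of about 85% would be needed to restore 80% power for a 20-point difference. The point also does not depend on anything left to another document, because it compares two statements printed in this one. Assuming that therapy cannot increase surgery does not narrow a 95% CI.

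**Conclusion.** The concern holds. The sizing rule and the reporting rule do not match. With 180 randomised, 20% dropout and 70% against 50%, power for the planned 95% CI is 69–71% (exact 69.6%), about 10 points below the stated 80%. The chance of missing a true 20-point reduction is about 30% instead of 20%.

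This rests on reading the unqualified 95% CI as two-sided, on the article's own dropout and control rate, and on no allowance for clustering. Full ascertainment or a markedly higher control rate would shrink the gap, but the article's power statement assumes neither.

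**What to change.** Keep the two-sided 95% CI as the primary analysis and correct the power statement, for example:

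*With 180 randomised and 20% dropout (72 evaluable per arm), power is about 70% to detect surgery rates of 70% and 50% at a two-sided 5% level; 80% power applies to a difference of about 22 to 23 percentage points.*

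If the sponsor does intend a one-sided 5% test, the statistical analyses section should say so and present the matching 90% CI for the primary odds ratio. Whichever is chosen should be fixed before unblinding and stated in the same terms in both sections.

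The cost is wording only. No participants are added and the model is unchanged, but the first option makes the stated power less favourable. Restoring 80% two-sided power for 20 points would instead take about 228–234 randomised, which is 48–54 more than planned.

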### Statistical analyses

The main treatment analysis will be conducted blinded to treatment allocation and will be analysed on an intention-to-treat basis with all randomized participants retaining their original randomized group. In the analysis of the primary outcome, the number of participants in each group who have received surgical treatment after 2 years will be compared using binary mixed models logistic regression and presented as odds ratios with a 95% CI.

We will also use mixed Cox proportional hazard models to describe and compare time to operation in the two groups, including establishment of the vital assumption of proportionality of the hazard rates.

In terms of secondary and tertiary outcomes, differences in mean values with 95% CI at each follow up will be analysed using mixed models analysis of covariance, adjusting for baseline levels of the outcome measure, while generalized linear mixed models will be used to estimate the overall effect for the total 2-year trial period, adjusting for the effect of clustering and repeated measures over time.

The assessment of the psychometric properties of MAP-Hand (research question 4) will adhere to the methods recommended by the international COSMIN group, using Kappa and ICC for examining test-retest reliability, and an anchor-based approach (based on the five-point global rating scale) to determine the minimal important change [62]. The smallest detectable change will be assessed by examining limits of agreement of repeated measures, computed as ± 1.96 SD of the difference between baseline scores and retest scores. The results from participants who report change in disease activity between baseline and rescoring will be excluded from the analysis of test-retest reliability and the smallest detectable change.

To assess the cost-effectiveness, we will need to estimate health outcomes and costs. The health outcomes will be measured using the EQ-5D and the costs will include the cost of the two interventions. This comprises the hours and frequency of occupational therapy, costs related to the provision of assistive devices, orthoses, and exercise material, and costs related to the surgical procedures, including post-operative treatment. Furthermore, costs related to medical or technical equipment purchased by participants and to the use of other health care services (home care services, rehabilitation, and institution) will be recorded for both the intervention and control group during the trial period.

Standard methods for economic evaluation will be applied and the cost-effectiveness will be calculated as the incremental cost-effectiveness ratio, which is defined by the cost per incremental QALY.

The level of significance will be set to 0.05 and we will use IBM SPSS Statistics 21 (IBM Corporation), R (R Core Team (2016). R: A language and environment for statistical computing. R Foundation for Statistical Computing, Vienna, Austria.) and Statistical Analysis System (SAS Institute Inc., Cary, NC, USA).

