### Outcome measures

The primary outcome will be the number of participants in each group who have received surgical treatment after 2 years.

Secondary and tertiary study outcomes are documented in Table 4 and are based on previously validated measures.

**Table 4 Tab4:** Secondary and tertiary outcome measures

	Data collection instrument and scale	Time points
Secondary outcome measures:		
Activity performance	MAP-Hand, mean of 18 standardized and up to five patient specific activities, respectively, rating scale 1–4, 1 is no problems	t1, t2*, t3, t4, t5
Physical function and symptoms in the arm, shoulder and hand	Quick-Dash, sum-score range 1–100, 1 = good function	t1, t3, t4, t5
Current situation with regards to main reason for wanting surgery	Numeric rating scale: 0–10, 0 is as bad as could be	t1, t3, t4, t5
Pain at rest	Numeric rating scale: 0–10, 0 is no pain. Both hands.	t1, t3, t4, t5
Grip strength	In Newton by the Grippit; maximum, mean and last of 20 recordings over a 10 s interval, both hands	t1, t3, t4, t5
Pain following measure of grip strength	Numeric rating scale: 0–10, 0 is no pain, both hands	t1, t3, t4, t5
Tertiary outcomes:		
Current pain in thumb selected for surgery	Numeric rating scale: 0–10, 0 is no pain	t1, t3, t4, t5
Painful finger joints	Examination by a trained OT of presence of pain yes/no in CMC1, MCP, PIP and DIP-joints in both hands	t1, t3, t4, t5
Finger flexion	Flexion deficit in millimetre of the II, III, IV and V finger of both hands	t1, t3, t4, t5
Range of motion thumb MCP	In degrees by a goniometer, both hands	t1, t3, t4, t5
Range of motion thumb IP	In degrees by a goniometer, both hands	t1, t3, t4, t5
Palmar abduction thumb	In degrees by a pollexograph, both hands	t1, t3, t4, t5
Abduction CMC1	In degrees by a pollexograph, both hands	t1, t3, t4, t5
Pinch strength	In Newton by the Grippit; maximum, mean and last of 20 recordings over a 10 s interval, both hands	t1, t3, t4, t5
Pain following measure of pinch strength	Numeric rating scale: 0–10, 0 is no pain, both hands	t1, t3, t4, t5
Pain following exercising	Exercise diary, numeric rating scale: 0–10, 0 is no pain	t3
Satisfaction with HOA care at current centre	Numeric rating scale: 0–10, 0 is very dissatisfied	t3, t4, t5

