Main reason for wanting surgery	Description of the main reason	t1
Previously received hand therapy due to HOA	Yes/no, if yes-what kind of therapy	t1
Motivation for surgery	Numeric rating scale: 0–10, 0 is no motivation	t1
Joints with osteoarthritis (as diagnosed by physician or finger joints with bony enlargement)	Marked by the OT on a map with joints of the body	t1
Degree of CMC1-HOA	Conventional radiography of both hands, graded according to the Kellgren-Lawrence method, with grades from 0 to 4, (grade 4 indicating large osteophytes, severe sclerosis and narrowing joint space)	
Degree of radial trapeziometacarpal subluxation	Conventional radiography of both hands, graded as subluxation ratio using a digital calculation calliper	
Presence of erosive HOA	Conventional radiography of both hands, ≥1 joint with erosion = erosive OA.	
Comorbidity	Presence of 16 diseases/health problems (yes/no)	t1
Comfort with use of assistive devices	Numeric rating scale: 0–10, 0 is very uncomfortable	t1, t3, t4, t5

t1 = baseline, t2* = two weeks after baseline (control group only), t3 = 4 months after baseline, t4 = 18 months after baseline, t5 = 24 months after baseline, *CMC1* Carpometacarpal joint of the thumb, *HOA* Hand osteoarthritis

Participants in the intervention group will report treatment adherence in the treatment period between baseline and 4 months in a treatment diary (see Tables 1 and 5).

To be able to describe and compare participants, we will, at baseline, record the participants’ age, gender, marital status, employment status, level of education, hand dominance, other diseases or previous injuries that may negatively impact hand function, previous hand surgery, in which hand they are referred for surgery, previous hand therapy, main reason for wanting surgery, motivation for surgery, current medication taken for HOA, and joints with osteoarthritis (including interphalangeal joints with bony enlargement in each hand). The degree of CMC1-OA and trapeziometacarpal subluxation and the presence of erosive HOA will be evaluated based on radiographs taken in relation to referral to surgical evaluation (Table 5) [61].

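### The primary result is planned only as an odds ratio, from a logistic model with no named baseline predictor or cluster unit, although the trial asks about and is sized on a 20-point difference in surgery proportion

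*Protocol article*

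**What the plan says.** Under Outcome measures: "The primary outcome will be the number of participants in each group who have received surgical treatment after 2 years". The first research question, under Aims and research questions, is likewise about the share of patients operated on.

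Under Statistical analyses, the groups "will be compared using binary mixed models logistic regression and presented as odds ratios with a 95% CI". No covariate is listed for this model, and the unit of the random effect is not named. Secondary and tertiary outcomes are analysed "adjusting for baseline levels of the outcome measure".

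Under Sample size calculations, the trial is built "To be able to detect a difference of 20% in surgery rate between the groups", assuming that "at least 70% of those who are currently deemed eligible for surgery will undergo operations", as a "one-sided calculation".

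Under Data collection, the surgeon's conclusion rests on symptoms, functional limitation and degree of CMC1-OA. Table 5 records motivation for surgery at baseline ("Numeric rating scale: 0–10, 0 is no motivation") and Kellgren-Lawrence grade 0 to 4. The stated purpose of these baseline data is description and comparison of participants.

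**The concern.** There are two gaps between the design and the stated primary analysis.

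- **Effect measure.** The question and the sizing are on the absolute scale, but the only planned estimate is an odds ratio. One odds ratio corresponds to different absolute differences at different control rates, and the article fixes the control rate only as at least 70%. With half or more of participants operated on, the odds ratio is also far from the risk ratio and easily misread as one.
- **Adjustment.** The article itself identifies what drives the decision to operate, and those variables are recorded. Leaving them out of the primary model gives up precision at no saving. Leaving them unnamed invites a choice of covariates after the data are seen.

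At stake are how clearly the main result answers the trial's question and a possible gain in power. The validity of the test is not at stake.

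**Working it through.** **1. Reproducing the sample size.** Inputs from Sample size calculations: 70% v 50%, one-sided 0.05, power 80%, dropout 20%.

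n per arm = (1.645 + 0.842)² × (0.70×0.30 + 0.50×0.50) / 0.20² = 6.18 × 0.46 / 0.04 = 71.1, so 72. Then 72 / 0.80 = 90 per arm, 180 in total. This matches. The 20% is therefore an absolute difference, and the calculation includes no covariate or clustering term.

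**2. What the odds ratio says about the target.** OR = (0.50/0.50) / (0.70/0.30) = 0.43, while the risk ratio is 0.50/0.70 = 0.71. Holding OR = 0.4286, intervention odds = control odds × 0.4286:

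| Control rate | Intervention rate | Difference (points) |
|---|---|---|
| 30% | 15.5% | 14.5 |
| 60% | 39.1% | 20.9 |
| 70% | 50.0% | 20.0 |
| 80% | 63.2% | 16.8 |
| 90% | 79.4% | 10.6 |

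For scale, the crude risk difference with 72 per arm has a 95% half-width of 1.96 × √(0.46/72) = 15.7 points.

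**3. Value of one baseline predictor.** Simulation with 72 analysed per arm, marginal rates fixed at 70% and 50%, and 4,000 trials per setting (Monte Carlo error about 0.6 points). Prognostic strength is an assumption, because the documents give none.

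| Assumed OR per SD | One-sided power, unadjusted → adjusted | Two-sided power, unadjusted → adjusted | Variance of standardised risk difference, relative to crude |
|---|---|---|---|
| 1.0 | 78% → 78% | 67% → 67% | 1.00 |
| 1.65 | 81% → 81% | 70% → 72% | 0.96 |
| 2.2 | 80% → 83% | 69% → 73% | 0.89 |
| 2.7 | 80% → 85% | 70% → 77% | 0.84 |
| 4.5 | 82% → 91% | 71% → 83% | 0.73 |

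The true unadjusted power is the same in every row, so its spread is simulation noise. The gain within a row is the useful figure.

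**4. Does a random centre intercept harm the treatment test?** Assume the unit is centre (three centres, 24 analysed per arm in each) and the between-centre SD on the logit scale is 0, 0.3, 0.5 or 1.0. In 600 maximum-likelihood fits per setting, the SD was estimated as essentially zero in about 77%, 54%, 35% and 13% of data sets. Yet one-sided type I error stayed at 5.0 to 6.2%, and power was within about 2 to 3 points of a model without centre.

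**5. Can the data carry the added terms?** Expected operated: 72×0.70 + 72×0.50 = 86.4. Not operated: 144 − 86.4 = 57.6. Arm, two centre terms, motivation and grade are five parameters, so about 57.6/5 = 11.5 participants in the smaller outcome class per parameter.

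**The case against.** The strongest reply is that this is a condensed article. Covariate lists are commonly left to an analysis plan that is not shown, an odds ratio is the usual output of logistic regression, and the crude difference follows from the group counts. Much of this stands, and it rules out several stronger readings.

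- A reader might infer that the sponsor chose an unadjusted primary analysis. The article is silent on covariates, and silence is not a decision.
- A reader might see an inconsistency with the secondary outcomes. There is none: those are adjusted for their own baseline value, and surgery received has no baseline value.
- A reader might infer that a random intercept on three centres costs precision. The article does not say the unit is centre; therapist or surgeon is also possible. If it is centre, the variance is poorly estimated but the treatment test is hardly affected (step 4).
- A reader might say the odds ratio itself loses power. It does not.
- A reader might extend the point to the Cox and continuous-outcome models. No calculation supports that.

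It is also fair to say that radiographic grade may be a modest predictor: the section on surgery for carpometacarpal OA notes that symptoms need not match radiographic stage.

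Two things are left. The effect measure is stated, not merely omitted, and it is not the one the trial was sized on. A crude difference can be rebuilt from counts, but a covariate-adjusted one with its interval has to be planned.

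**Conclusion.** The point holds as an improvement to the stated analysis, not as an error that invalidates it. The mismatch of scale is documented: at an odds ratio of 0.43 the absolute difference falls from 20 points to 10.6 as the control rate rises from 70% to 90%.

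The gain from adjustment is conditional. It runs from nil to about 9 points of one-sided power (about 12 two-sided), with the variance of the risk difference falling by 0 to 27%, over assumed predictor odds ratios of 1.0 to 4.5 per SD. At 2.2 to 2.7 it is about 3 to 5 points one-sided. These figures assume 72 analysed per arm, true rates of 70% and 50%, and a single normally distributed predictor. In no setting did adjustment lose more than simulation noise.

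Pairing a one-sided calculation with a 95% CI, which corresponds to a two-sided test (about 69% power with 72 per arm), is a separate matter and is not part of this conclusion.

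**What to change.** In Statistical analyses, specify the primary model as logistic regression on arm, baseline motivation for surgery (0–10), radiographic CMC1-OA grade, and centre as a three-level factor. Report the standardised risk difference with 95% CI beside the odds ratio: average the predicted probability of surgery over all analysed participants under each arm, and take the difference. Keep the unadjusted analysis as a sensitivity analysis.

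The cost is wording, with no new data collection. There are two small downsides.

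- The adjusted odds ratio is conditional and lies further from 1 than the crude one. In the simulation, a marginal 0.43 corresponds to about 0.38 at a predictor odds ratio of 2.2 and 0.36 at 2.7. This is a further reason to show the risk difference.
- Radiographs come from referral, not from the baseline visit, and their completeness is not stated. A simple rule for missing grades, fixed without sight of allocation, is needed.
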